### **Secondary**

1. To determine the effect of HCQ on the clinical course and duration of the COVID-19 disease in SARS-CoV-2-infected pregnant women.
2. To determine the impact of HCQ on the risk of hospitalization and mortality of SARS-CoV-2-infected pregnant women.
3. To assess the safety and tolerability of HCQ in pregnant women.

4. To describe the clinical presentation of SARS-CoV-2 infection during pregnancy.
5. To describe the effects of maternal SARS-CoV-2 infection on pregnancy and perinatal outcomes by treatment group.
6. To determine the risk of vertical transmission (intra-utero and intra-partum) of SARS-CoV-2.

## 5. Methods

### a. Study design

This is a randomized controlled clinical trial.

#### Study sites

The trial will be conducted in five hospitals in Spain: the Hospital Clínic of Barcelona, the Hospital Sant Joan de Déu and the Hospital de la Santa Creu i Sant Pau, in Barcelona, and the HM Puerta del Sur and Hospital Universitario de Torrejón, in Madrid. Madrid and Catalonia are the two regions more severely affected by the COVID-19 pandemic in Spain, with 56963 and 41676 reported cases respectively at date 20th April 2020 (20).

#### Trial design

The trial has been designed as a randomized double-blind placebo-controlled multicentre trial to evaluate the safety and efficacy of HCQ to prevent and/or minimize SARS-CoV-2 infection during pregnancy. A total of 714 pregnant women are expected to participate in the study (see sample size calculation).

The study participants will be stratified by clinical presentation and SARS-CoV-2 PCR results. The following are the study groups:

- **SARS-CoV-2-PCR confirmed, infected** pregnant women:
  - a. *symptomatic* (n=100)
  - b. *asymptomatic* (n=100)
- **SARS-CoV-2 PCR negative** pregnant women in **contact** with a SARS-CoV-2-infected confirmed or suspected case (n=514).

Women in each group will be randomly allocated to receive either HCQ or placebo. Evaluations will include safety and tolerability, SARS-CoV-2 PCR and COVID-19 clinical diagnosis and presentation, as well as neonatal SARS-CoV-2 by PCR and IgM/IgG.

#### Primary endpoint

Number of PCR-confirmed infected pregnant women assessed from collected nasopharyngeal and oropharyngeal swabs at day 21 after treatment start (one week after treatment is completed).

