## **4. Objectives**

### **Primary**

1. To assess the effect of HCQ in reducing SARS-CoV-2 viral shedding by PCR in infected pregnant women with mild symptoms.
2. To assess the efficacy of HCQ to prevent incident SARS-CoV-2 infection in pregnant women in contact with an infected or suspected case.
3. To evaluate the effect of HCQ in preventing the development of the COVID-19 disease in asymptomatic SARS-CoV-2-infected pregnant women.

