#### Secondary endpoints

##### Maternal/Foetal

1. Incidence of COVID-19 disease during pregnancy
2. Incidence of COVID-19-related admissions
3. Incidence of all-cause admissions
4. Incidence of all-cause outpatient attendances
5. Mean duration of symptoms-signs of COVID-19

6. Frequency and severity of adverse events
7. Incidence of preeclampsia
8. Incidence of gestational diabetes
9. Incidence of SARS-CoV-2 infections during pregnancy
10. Prevalence of intrauterine growth restriction (<10th centile according to local standards) (21)
11. Maternal mortality rate

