##### **e) SARS-CoV-2 testing**

A nasopharyngeal and oropharyngeal swabs of all included women will be collected for SARS-CoV-2 diagnosis by PCR. Additionally, 5 ml of venous blood will be collected for SARS-CoV-2 serologic analysis of all participants at baseline.

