#### **Household and follow-up visits**

At day 21 after initiating study drugs' administration (one week after treatment completion), study personnel will visit women at home or at the hospital to collect a nasopharyngeal and oropharyngeal swabs for PCR -SARS-CoV-2 and to perform an ECG.

The study personnel will assess treatment adherence by requesting and counting if there are remaining study pills.

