| Demographics/medical history                                                                                                                                                      | x                           |                                            |                                                               | x                      |                                      |                             |
| Physical/clinical examination                                                                                                                                                     | x                           |                                            |                                                               | x                      |                                      |                             |
| Concomitant medication                                                                                                                                                            | x                           |                                            | x                                                             | x                      | x                                    |                             |
| Gestational age                                                                                                                                                                   | x                           |                                            | x                                                             | x                      | x                                    |                             |
| 
 
Nasopharyngeal and oropharyngeal swabs for maternal SARS-CoV-2 PCR
 
Venous blood (5 ml, IgG and IgM against SARS-CoV-2)
 
 | x                           |                                            | x                                                             |                        |                                      |                             |
| Maternal and perinatal outcome                                                                                                                                                    |                             |                                            |                                                               |                        | x                                    |                             |

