| Adherence to study medication                                                                                                                                                     |                             | x                                          | x                                                             |                        |                                      |                             |
| Ultrasound data                                                                                                                                                                   |                             |                                            |                                                               | x                      |                                      |                             |
| Infant health status check (telematics visit)                                                                                                                                     |                             |                                            |                                                               |                        |                                      | x                           |

\* In case of presence of fever and/or two symptoms suggestive of COVID-19 disease (fever, fatigue, cough (with or without sputum production), anorexia, malaise, muscle pain, sore throat, dyspnea, nasal congestion, or headache, diarrhoea, nausea and vomiting) in the previous 14 days, women will be collected a nasopharyngeal and oropharyngeal swabs for PCR analysis at any time.

\*\*In a sub-sample of participants (n=120).

\*\*\*12-24 hours of life.

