#### **Statistical models and methods of analysis**

The primary analysis of the trial will be:

- The comparison of the proportion of negative SARS-CoV-2 PCR at day 14 after initiating treatment administration among those women who were SARS-CoV-2 PCR positive at recruitment in the ITT and ATP cohorts.
- The comparison of the proportion of pregnant women who were negative SARS-CoV-2 PCR at recruitment and close contacts of confirmed cases of SARS-CoV-2 infection, with a positive PCR for the infection at day 14, in the ITT and ATP cohorts.

Proportions will be compared between the two intervention-arms within each group using the Fisher exact test and presented as relative risk ratio (RR) or reduction of the RR ( $1 - RR * 100\%$ ) if RR lower than 1. Adjustment for co-variables and possible confounders will be done using Poisson regression with a log link and robust estimate of the covariance (Huber method), using the method proposed by Zou et al. 2014 and 2013.

Continuous variables will be compared between groups using Wilcoxon rank sum test and the effect presented as Mean Difference. Adjustment for co-variables and possible cofounders will be done using ordinary least square regression. Variables will be transformed to the logarithm scale if normality is improved and results presented as Proportional Difference. If after transformation, non-normality of the residuals is detected using diagnostic regression plots, robust intervals of confidence and Wald test will be presented instead.

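### The primary endpoint and primary analysis score PCR-negative contacts on a single day, so they measure point prevalence, not the incident infection named in Objective 2, and cannot separate prevention from faster clearance

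*Protocol*

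**What the plan says.** All references are to the Protocol.

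- **Objectives, Primary, no. 2:** "To assess the efficacy of HCQ to prevent incident SARS-CoV-2 infection in pregnant women in contact with an infected or suspected case".
- **Primary endpoint:** one definition for all three study groups, "Number of PCR-confirmed infected pregnant women assessed from collected nasopharyngeal and oropharyngeal swabs at day 21 after treatment start".
- **Statistical models and methods of analysis:** women PCR-negative at recruitment are compared on the proportion "with a positive PCR for the infection at day 14, in the ITT and ATP cohorts".
- **Household and follow-up visits:** the swab visit is described thus: "At day 21 after initiating study drugs' administration (one week after treatment completion), study personnel will visit women at home or at the hospital". Table 1 marks maternal swabs at enrolment and at this visit only, with none in the intervention-period column.
- **Table 1 footnote:** if fever and/or two listed symptoms occur, "women will be collected a nasopharyngeal and oropharyngeal swabs for PCR analysis at any time". Nothing in the Protocol says whether such a positive counts toward the primary endpoint.
- **Secondary endpoints, Maternal/Foetal, no. 9:** "Incidence of SARS-CoV-2 infections during pregnancy".
- **Hypotheses:** in infected symptomatic women, the drug is expected to reduce viral shedding by PCR.
- **Sample size:** 257 contacts per arm, with 3% infected in the control group after two weeks. The Protocol calls this 3% a prevalence.

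**The concern.** Incident infection is cumulative: a woman who becomes infected during follow-up has had the event whether or not she is still shedding later. A swab on one day records only who is positive on that day. A contact confirmed positive on day 6 by a symptom-triggered swab and negative on day 21 is, on the literal wording, a prevention success.

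This would matter less if clearance were unrelated to treatment. Here the drug is itself hypothesised to shorten shedding. If that hypothesis is true, fewer treated women will be positive on the scored day even if exactly as many were infected. The prevention result could then reflect clearance, and the primary analysis has no means of telling the two apart. Events would also go uncounted in a comparison that expects very few of them.

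**Working it through.** **1. The planned figure.** Inputs from Sample size: 3% versus 0%, two-sided 0.05, 80% power. The pooled normal approximation without continuity correction gives 257 per arm, which matches the Protocol (power 80.1%). With the planned Fisher exact test, 6 versus 0 events gives p = 0.030 and 5 versus 0 gives p = 0.061, so against complete prevention at least 6 control events are needed. Expected control events are 257 × 0.03 = 7.7. Fisher power is P(Bin(257, 0.03) ≥ 6) = 78.5%.

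**2. How clearance enters the estimate.** Let s_T and s_C be the shares of infected women in the treated and control arms who are still PCR-positive on the scored day. Then

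apparent RR = true RR × (s_T / s_C).

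The Protocol gives no value for either share, so these are assumptions, all with true RR = 1.00 (no prevention):

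| s_T | s_C | apparent RR |
|---|---|---|
| 0.60 | 0.60 | 1.00 |
| 0.40 | 0.60 | 0.67 |
| 0.40 | 0.80 | 0.50 |
| 0.30 | 0.60 | 0.50 |
| 0.15 | 0.60 | 0.25 |

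**3. How often clearance alone would give significance.** Exact Fisher probabilities at 257 per arm, no prevention:

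| cumulative infection, both arms | still positive, control vs treated | observed rates | P(significant) |
|---|---|---|---|
| 3% | 60% vs 60% | 1.8% vs 1.8% | 2.0% |
| 3% | 60% vs 30% | 1.8% vs 0.9% | 5.9% |
| 3% | 80% vs 40% | 2.4% vs 1.2% | 9.3% |
| 10% | 80% vs 40% | 8% vs 4% | 41.9% |
| 20% | 80% vs 40% | 16% vs 8% | 76.7% |

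**4. Power, conditional on what the 3% means.** If 3% is cumulative infection and only 80%, 60% or 50% of control infections are still positive, the observed control rate is 2.4%, 1.8% or 1.5%. Fisher power against complete prevention is then 58.3%, 31.8% or 19.1%. If 3% is already the proportion positive at assessment, no discount applies and power stays at 78.5%. The cost is then only that extra events which could have been counted are not.

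**5. The two sections against each other.** The endpoint says day 21 and the analysis says day 14. The only scheduled post-baseline maternal swab is on day 21. Reconciling the days is necessary but does not cure the problem, since either is a single-day status.

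**The case against.** **The cumulative measure is already there.** Secondary endpoint 9 is an incidence, so a reader who infers that early infections are lost to the trial goes too far: they are recorded. But the endpoint is secondary and runs over the whole pregnancy, so it does not define the primary comparison through day 21.

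**The harm can be overstated.** A reader might infer that the trial is likely to make a false claim of prevention. At the planned 3% that is not supported: even a halving of the share still positive yields significance in about 9% of trials. A reader might also infer that power falls to 58% or 19%. The Protocol calls the 3% a prevalence, so applying a clearance discount may count the same loss twice. Both points stand.

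**A single scheduled swab gives equal ascertainment in both arms.** Symptom-triggered testing does not. The listed triggers include diarrhoea, nausea and vomiting, which the HCQ side effects section names as drug effects, and the drug may also suppress COVID-19 symptoms. Testing could differ by arm in either direction. This is a real cost of a cumulative endpoint and calls for sensitivity analyses.

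**Serology looks like the complete answer.** A reader might infer that seroconversion belongs in the primary event because paired samples are planned. The documents do not settle that. Table 1 puts "Venous blood (5 ml, IgG and IgM against SARS-CoV-2") in one row with the swabs, with shared marks at enrolment and the post-treatment visit, while the text says "5 ml of venous blood will be collected for SARS-CoV-2 serologic analysis of all participants at baseline" and the day-21 visit description lists no blood draw. The main assay is described as still in development. Exposure may precede enrolment by up to 14 days, so seroconversion can reflect infection acquired before randomisation. Nor do women seropositive at baseline bias the comparison: randomisation spreads them over both arms, and they cost some power.

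**Conclusion.** The point holds as a mismatch between an incidence objective and a single-day endpoint and analysis, made worse by a drug hypothesised to act on clearance, and by a day-14 versus day-21 contradiction between the two sections. Followed literally, the primary analysis cannot attribute a lower proportion positive to prevention.

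The size is uncertain. The direction of bias follows from the Protocol's own shedding hypothesis. Its amount depends on clearance shares that the Protocol does not give; halving the share still positive would produce an apparent RR of 0.50 with no prevention. At the planned 3% rate the main harm is a biased estimate and uncounted events, with a clearance-only significant result uncommon (about 9% in that example, rising if infection is more frequent than planned). The loss of power applies only if the 3% is read as cumulative infection.

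**What to change.** For the contact stratum, define the primary event as any positive SARS-CoV-2 PCR, scheduled or symptom-triggered, after baseline and up to and including the day-21 visit. Put that same definition and window in both Primary endpoint and Statistical models and methods of analysis, which removes the day-14 conflict.

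Add two sensitivity analyses: day-21 PCR alone, which keeps equal ascertainment in both arms, and one excluding events found only through swabs triggered by gastrointestinal symptoms alone. Report seroconversion and the restriction to baseline-seronegative women as supportive only, after Table 1, the SARS-CoV-2 testing section and the day-21 visit description are made to agree on whether blood is drawn at day 21.

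The cost of the primary change is wording, since the swabs are already planned; the day-21 blood draw may be an addition. The remedy is partial: infections without symptoms that clear before day 21 will still be missed by PCR, and ascertainment of the rest depends on symptoms.

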#### Secondary endpoints

##### Maternal/Foetal

1. Incidence of COVID-19 disease during pregnancy
2. Incidence of COVID-19-related admissions
3. Incidence of all-cause admissions
4. Incidence of all-cause outpatient attendances
5. Mean duration of symptoms-signs of COVID-19

6. Frequency and severity of adverse events
7. Incidence of preeclampsia
8. Incidence of gestational diabetes
9. Incidence of SARS-CoV-2 infections during pregnancy
10. Prevalence of intrauterine growth restriction (<10th centile according to local standards) (21)
11. Maternal mortality rate

#### *Infant*

1. Proportion of neonates with SARS-CoV-2- intrauterine infection by PCR-confirmed SARS-CoV-2-infection in nasopharyngeal aspirate.
2. Proportion of neonates with clinical signs/symptoms of COVID-19
3. Prevalence of low birth weight (<10th centile according to local standards) (21)
4. Prevalence of preterm birth (<37 weeks of gestational age)
5. Prevalence of embryo and foetal losses (miscarriages and stillbirths)
6. Frequency of congenital malformations
7. Proportion of adverse perinatal outcome
8. Neonatal morbidity
9. Neonatal mortality rate

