**b) Placental sample collection**

In a sub-sample of study participants (n=120, randomly selected from the three study groups), a placental sample will be collected for histological examination. Within minutes of placental expulsion, the fetal surface of the placenta will be disinfected and incised with a sterile scalpel, and 2 swabs and biopsies (close to the umbilical cord and peripheral margin) will be obtained.

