**c) New-born assessments**

A 5 ml blood sample for SARS-CoV-2 for Ig G and Ig M determination will be collected from the umbilical vein once the baby's umbilical cord has been cut and clamped. Information on the new-born anthropometrical parameters and clinical status will be recorded onto the study eCRF.

A nasopharyngeal aspirate will be collected 12 to 24 hours after birth for PCR- SARS-CoV-2 infection assessment.

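### One neonatal PCR at 12–24 hours is labelled intrauterine infection, so infant endpoint 1 cannot give the two route-specific risks in secondary objective 6

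*Protocol*

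**What the plan says.** Protocol section 4 (Objectives, Secondary), item 6, is "To determine the risk of vertical transmission (intra-utero and intra-partum) of SARS-CoV-2". The matching outcome in section 5.a (Secondary endpoints, Infant), item 1, is the "Proportion of neonates with SARS-CoV-2- intrauterine infection by PCR-confirmed SARS-CoV-2-infection in nasopharyngeal aspirate". Section 5.c (New-born assessments) fixes the sample: "A nasopharyngeal aspirate will be collected 12 to 24 hours after birth for PCR- SARS-CoV-2 infection assessment". A footnote to Table 1 repeats the window.

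Other material bearing on neonatal infection is collected but is not part of the endpoint:

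- Cord blood: "A 5 ml blood sample for SARS-CoV-2 for Ig G and Ig M determination will be collected from the umbilical vein". Section 5.a (Trial design) lists among the evaluations "as well as neonatal SARS-CoV-2 by PCR and IgM/IgG".
- Placenta, in a random sub-sample of 120: "2 swabs and biopsies (close to the umbilical cord and peripheral margin) will be obtained". Histology is the only stated purpose (sections 5.c and 5.d, Table 1).

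Table 1 marks the row "Nasopharyngeal and oropharyngeal swabs for maternal SARS-CoV-2 PCR" at enrolment and at the visit 7 days after treatment, not at delivery. A footnote adds symptom-triggered maternal PCR at any time. The largest study group consists of PCR-negative "pregnant women in contact with a SARS-CoV-2-infected confirmed or suspected case (n=514").

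**The concern.** The objective names two routes and the endpoint has one category. That category is assigned from an airway sample taken after labour, delivery and up to a day of postnatal contact. A newborn who acquired the virus during or after birth would be counted as an intrauterine infection, and the intra-partum half of the objective has no endpoint.

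The label matters because of the protocol's own Background. It says that intrauterine transmission of SARS and MERS has not been documented, and that newborns in the few COVID-19 reports tested negative. Against that, even one or two mislabelled positives would be read as evidence of intrauterine transmission.

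**Working it through.** **1. Can the endpoint separate the routes?** Let *a*, *b* and *c* be the numbers of PCR-positive neonates who acquired the virus in utero, intra-partum and early postnatally. The endpoint observes only the sum *a + b + c* and reports all of it as *a*. Suppose there are 6 positives (an illustrative number). Then (6, 0, 0), (3, 3, 0) and (0, 2, 4) all give the same value, although the true intrauterine count is 6, 3 or 0. One observed number cannot fix two route-specific risks.

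**2. Does another endpoint fill the gap?** Infant endpoint 2 counts clinical signs and symptoms, without regard to route. The remaining seven concern birth weight, prematurity, losses, malformations, adverse perinatal outcome, morbidity and mortality. None addresses intra-partum transmission.

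**3. Do the planned samples bear on timing?** Cord blood is drawn once the cord is clamped and cut, so it precedes most postnatal exposure. Placental material does too, but only in 120 women and for histology. Data bearing on timing therefore exist. What is missing is a rule that uses them.

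**4. Is maternal infection known near delivery?** Enrolment is possible from just after 12 weeks. Day 21 then falls at about 12 + 3 = 15 weeks. A birth at 37 weeks, the protocol's own limit for preterm birth, comes 37 − 15 = 22 weeks later. In between, only symptom-triggered swabs are available, so asymptomatic maternal infection can be missed.

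**5. Denominator, under a pooled reading only.** The endpoint says neonates, without restriction by maternal infection. The protocol states no figure for this endpoint. The figure that sets the uninfected share is 257 contacts per arm (section 5.a, Sample size), and it reproduces for 3% against 0%, two-sided 0.05, 80% power:

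n = [1.960·√(2·0.015·0.985) + 0.842·√(0.03·0.97)]² / 0.03² = (0.337 + 0.144)² / 0.0009 ≈ 257, so 514 in all.

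Infected mothers, assuming one neonate per woman, no losses and no maternal infection after day 21:

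| Counted as infected | Mothers | 714 / mothers | Shown if true risk is 1% | 3% | 5% |
|---|---|---|---|---|---|
| Infected at entry only | 200 | 3.57 | 0.28% | 0.84% | 1.40% |
| Plus 3% of 257 control contacts | 207.7 | 3.44 | 0.29% | 0.87% | 1.45% |
| Plus 3% of all 514 contacts | 215.4 | 3.31 | 0.30% | 0.91% | 1.51% |

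The true risks are assumed for illustration. They correspond to about 2, 6 and 10–11 positive neonates.

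**The case against.** The best defence is that this is one of nine infant secondary endpoints serving the last of six secondary objectives. The label applies equally in both arms, and nothing in the primary analysis depends on it. That stands, and it limits the weight of the point.

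Three stronger readings are tempting, and the protocol does not support them.

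- *The reported risk will be diluted more than threefold.* The endpoint does not say that all 714 neonates are pooled. Section 5.i (Statistical models and methods of analysis) compares proportions between arms inside each group. If that is applied to infant outcomes, neonates of the 200 women infected at entry are tabulated apart from those of the 514 contacts. An analysis plan may also set the denominator. Maternal infection after day 21 would reduce the dilution further.
- *Timing can never be assessed.* Cord IgG and IgM are collected and are named among the trial's evaluations. The gap lies in the endpoint definition, not wholly in the data.
- *Mothers are not tested after day 21.* Symptomatic women are. Only asymptomatic infection goes unseen.

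It would also be too much to call the result uninterpretable. Neonatal PCR positivity at 12–24 hours, reported by maternal group, is a clear quantity under its own name.

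None of this removes the conflict between objective 6 and infant endpoint 1. Restricting the denominator would not separate the routes.

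**Conclusion.** The point holds as a mismatch between an objective and its endpoint. Infant endpoint 1 attaches an intrauterine label to a measurement that cannot establish it, and it would mislabel any intra-partum or early postnatal positive. It cannot deliver the two risks named in objective 6. This follows from the text alone and needs no assumed rate. The number mislabelled cannot be derived from the protocol.

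The 3.3 to 3.6 fold understatement is conditional on pooling all 714 neonates, on about 200–215 infected mothers, and on no maternal infection after day 21. It is a reason to state the denominator, not an established error. The correction should be made, but it concerns a secondary objective and leaves the primary comparison untouched.

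**What to change.** - Rename infant endpoint 1 as neonatal SARS-CoV-2 PCR positivity at 12–24 h.
- Report it for neonates of women with PCR-confirmed infection at any time from enrolment to delivery, separately from neonates of women with no documented infection.
- Tabulate it against cord-blood IgM and IgG as supportive evidence on timing. Class PCR-positive, cord-IgM-negative neonates as timing undetermined. Cord IgM should not be the sole criterion, because section 5.d describes the multiplex assay as still in development and gives no sensitivity or specificity.
- Restate objective 6 as overall perinatal transmission. Say that intra-partum risk cannot be isolated. Say also that asymptomatic maternal infection after day 21 may be missed, since no maternal swab is scheduled at delivery.

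The cost is wording and tabulation only, as the aspirate and cord serology are already planned. Viral testing of placental material is not required. It would be a new procedure, because only histology is planned. The price is a smaller denominator for the main figure and a more modest claim about route.

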#### **Sample size**

A sample size of 100 infected pregnant women of each asymptomatic and symptomatic group, 1:1 randomly allocated into two study arms, allows to detect an effect size of 30%, 34% and 39% with 80% power and two-tail type-I error of 0.05 assuming 3%, 10% and 30% curation rates in the control group, respectively. In other words, this sample allows detecting differences if the cure rates in the intervention group are at least 33%, 44%, and 69%, respectively. A sample size of 257 non-infected, contact positive, pregnant women per intervention arm will be needed to detect a 3 % reduction in the prevalence of infection with 80% power and two-tail type-I error of 0.05, assuming a prevalence of infection in the control group of 3% after two weeks of follow up.

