#### **b) Treatment arm allocation**

Participants will be then randomized in a 1:1 ratio to HCQ (400 mg/day for three days, followed by 200 mg/day for 11 days) or placebo (2 tablets for three days, followed by one tablet for 11 days).

Allocation of participants to study arms will be done centrally by the trial's Sponsor (the Barcelona Institute for Global Health, ISGlobal) by block randomization. This method will ensure balanced allocation to both arms. The electronic CRF will assign automatically a study number to each participant, depending on her study group and recruitment site. Each number will be related to a treatment number, which assigns them to one of the study arms. Randomizations lists with treatment assignment for each study participant will be concealed in opaque sealed envelopes and only open in case of urgent need following study unblinding procedures.

A study card will be given to the participant in order to facilitate their clinical management in case they attend primary care centres or other hospitals.

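### Both foetal growth endpoints are defined only as a proportion below the 10th centile, which costs about half the power if HCQ shifts birth weight modestly in all infants

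*Protocol*

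**What the plan says.** Protocol section 5.a lists two growth outcomes among its 20 secondary endpoints (11 maternal/foetal, 9 infant). Maternal/Foetal item 10 is "Prevalence of intrauterine growth restriction (<10 th centile according to local standards" and Infant item 3 is "Prevalence of low birth weight (<10 th centile according to local standards". Both cite the same reference, a customised Spanish birthweight standard. The only listed endpoint expressed as a mean is the duration of COVID-19 symptoms.

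On data capture, section 5.c (New-born assessments) states: "Information on the new-born anthropometrical parameters and clinical status will be recorded onto the study eCRF". Birth weight is not named there, but the endpoint needs it. Table 1 has gestational age recorded at delivery.

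On analysis, section 5.i has proportions compared between arms within each study group by Fisher's exact test and expressed as a relative risk. For other variables it says: "Continuous variables will be compared between groups using Wilcoxon rank sum test and the effect presented as Mean Difference". No growth endpoint is listed to which this second rule would apply. The same section has safety analysed by trial arm.

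Secondary objective 3 is the safety and tolerability of HCQ in pregnant women. Objective 5 is to describe perinatal outcomes by treatment group. The adverse-event monitoring section says safety is assessed in the foetus and newborn as well as the mother.

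**The concern.** A cut at the 10th centile uses only which side of the line each infant falls on. If a drug lowers birth weight slightly across the whole population, most of the movement happens among infants who stay above the line, and the proportion barely registers it. The trial would hold the measurements that could show such a shift, but its listed endpoints would not use them.

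What is at stake is how precise the trial's statement on foetal growth can be. A small, general effect could leave the relative risk with an interval too wide to say much, while the mean difference from the same newborns would be considerably more informative. The primary endpoint, the sample size and the efficacy conclusions are unaffected.

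**Working it through.** **Inputs from the protocol.** Trial design: "A total of 714 pregnant women are expected to participate in the study". Treatment arm allocation: "Participants will be then randomized in a 1:1 ratio to HCQ". This gives 714 / 2 = 357 per arm with the groups pooled. Sample size: "A sample size of 257 non-infected, contact positive, pregnant women per intervention arm will be needed". The infected groups have 100 women each, so 50 per arm. The sample-size section works "with 80% power and two-tail type-I error of 0.05"; I carry the two-sided 0.05 over to growth, for which the protocol states no power.

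**The plan's own figure.** The stated 257 per arm is for infection, 3% v 0%. With the pooled two-proportion formula the mean rate is 0.015, and
n = [1.960·√(2·0.015·0.985) + 0.842·√(0.03·0.97)]² / 0.03² = (0.3369 + 0.1436)² / 0.0009 = 256.5, so 257. The figure is reproduced, and the same test formula is used below.

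**Assumptions for growth (not in the protocol).** Birthweight z-scores are normal with SD 1, 10% of controls fall below the 10th centile, and HCQ lowers every infant's z-score by d.

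**Formulas.**
- Proportion below the cut on HCQ: p₂ = Φ(−1.2816 + d).
- Power of the cut: Φ{[(p₂ − 0.10) − 1.96·√(2p̄q̄/n)] / √[(0.09 + p₂q₂)/n]}, where p̄ is the mean of 0.10 and p₂, q̄ = 1 − p̄ and q₂ = 1 − p₂.
- Power of the z-score: Φ(d·√(n/2) − 1.96).

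**Worked case, d = 0.20, n = 357.** p₂ = Φ(−1.0816) = 0.1397.
- Cut: Φ[(0.0397 − 1.96·0.02431) / 0.02426] = Φ(−0.33) = 0.37.
- z-score: Φ(0.20·13.36 − 1.96) = Φ(0.71) = 0.76.

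**Range.**

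| Shift d (SD) | HCQ below cut | Cut, 357/arm | z-score, 357/arm | Cut, 257/arm | z-score, 257/arm |
|---|---|---|---|---|---|
| 0.10 | 11.9% | 0.123 | 0.266 | 0.100 | 0.204 |
| 0.15 | 12.9% | 0.227 | 0.518 | 0.176 | 0.398 |
| 0.20 | 14.0% | 0.372 | 0.762 | 0.283 | 0.621 |
| 0.25 | 15.1% | 0.541 | 0.916 | 0.416 | 0.809 |
| 0.30 | 16.3% | 0.705 | 0.980 | 0.563 | 0.925 |

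At d = 0.21 the z-score reaches 80% with 356 per arm, whereas the cut needs 947. At 357 per arm the cut has 40% there.

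**Sensitivity.**
- Planned tests, d = 0.20, 357 per arm: Fisher's exact gives 33% for the cut. The Wilcoxon test, with large-sample efficiency 3/π = 0.955 for a normal shift, gives Φ(0.20·√(0.955·357/2) − 1.96) = Φ(0.65) = 74%.
- 10% loss (321 per arm), d = 0.20: 34% v 72%.
- Control rate of 5% to 20% instead of 10%, d = 0.21, 357 per arm: the cut has 29% to 52%, the z-score 80%.
- Each infected group alone (50 per arm), d = 0.20: 9% v 17%, inadequate either way.

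**Harm in a subset (357 per arm).** If a fraction f of HCQ infants is shifted by s, then p₂ = 0.10(1 − f) + f·Φ(−1.2816 + s), the mean difference is f·s, and the variance on HCQ is 1 + f(1 − f)s². For f = 0.10 and s = 1.5, p₂ = 0.09 + 0.1·0.586 = 0.149, the mean difference is 0.15 and the variance is 1.2025.
- z-score: Φ(0.15 / √(2.2025/357) − 1.96) = Φ(−0.05) = 0.48.
- Cut: 0.50.

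Other patterns, cut v z-score:
- 10% of infants shifted 2 SD: 0.743 v 0.691.
- 15% shifted 1.5 SD: 0.812 v 0.803.
- 20% shifted 1 SD: 0.636 v 0.729.

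**The case against.** The strongest reply is that the protocol does nothing wrong here. The analysis section calls itself general and defers to an analysis plan still to be written, a continuous method is already stated, and nothing forbids applying it to birth weight. Prevalence below a named centile of a named standard is also clinically readable and fits an objective worded as description. Much of this stands. It keeps the point minor and rules out any suggestion that a continuous analysis is prohibited. It does not remove the point, because endpoint definitions belong to the protocol and both growth endpoints are fixed there as prevalences.

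The second reply is that the loss depends on the pattern of harm. This stands in full. The subset calculations show the cut matching or beating the z-score when a small fraction of infants is strongly affected. A reader might infer that the z-score should replace the cut at no cost. The figures do not support that, because demoting the proportion to a descriptive figure would weaken the comparison better suited to tail harm.

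Third, 357 per arm is not the comparison stated for proportions, which is within each study group. Pooling is plausible, since safety is analysed by arm, but it is an assumption. The contact-group figures are therefore given as well, and the relative loss there is similar.

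A reader might also infer that growth is a key safety outcome, or that a null result would be taken as reassurance. The protocol ranks growth only as secondary, and it states no such inference. It also plans to report a relative risk, not just a test.

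**Conclusion.** The point holds as a minor improvement. Both growth endpoints are fixed as proportions below the 10th centile, with no continuous growth measure beside them, although the required birth weight is implied by the recorded anthropometry. Under a modest uniform shift the cut has about half the power of the z-score, with a gap of 39 percentage points pooled and 34 in the contact group at 0.20 SD. The ratio narrows for larger shifts (0.705 v 0.980 at 0.30 SD, pooled), and the advantage disappears or reverses if harm is confined to a small subset.

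The size rests on assumptions the protocol does not supply: the shift, its uniformity, normal z-scores, and a local standard that places about 10% of controls below its 10th centile. A general claim that the cut halves the power to detect growth harm would go further than the documents allow.

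**What to change.** Extend Infant endpoint 3 so that it has two parts, each compared between arms:

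1. The birthweight z-score on the same local standard, analysed with the continuous methods already in section 5.i and reported as a mean difference with 95% CI.
2. The proportion below the 10th centile, kept as now and reported as a relative risk with 95% CI.

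State whether these are compared by arm overall, within each study group, or both. The foetal endpoint (Maternal/Foetal item 10) can stay as it is.

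The cost is a change of wording and one more secondary comparison. No new measurement, visit or sample is needed, provided birth weight is among the anthropometric items on the eCRF, which the existing endpoint already requires.
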